### Secondary objectives

Secondary objectives are to evaluate tumour response, performance status, biodistribution, quality of life and to compare the accuracy of the ^99m^Tc-MAA scout dose with a safety dose of ^166^Ho-PLLA-MS, in predicting microsphere distribution of the treatment dose. Tumour response will be quantified using CT of the liver scored according to Response Evaluation Criteria in Solid Tumours guidelines (RECIST 1.1) [27]. Tumour viability will be assessed by PET, depending on tumour type. In addition, the antitumoral effect will be assessed by relevant tumour markers responses if applicable (i.e. carcinoembryonic antigen (CEA) in colorectal carcinoma and chromogranin A (CgA) for neuroendocrine tumours). Biodistribution is assessed using quantitative SPECT and MRI. Urine and blood samples will be screened for presence of ^166^Ho-PLLA-MS or fragments of ^166^Ho-PLLA-MS. Performance status is assessed using WHO performance status criteria. Quality of life (QoL) is evaluated using the EORTC questionnaire QLQ-C30 with colorectal liver metastases module QLQ-LMC21. Finally, the accuracy of the ^166^Ho-PLLA-MS safety dose in predicting the distribution of the treatment dose is compared with the accuracy of the ^99m^Tc-MAA. Quantitative SPECT analysis will be performed using the scatter correction method described by De Wit *et al*. [14].

### Safety profile

From the literature on ^90^Y-RE, it is known that several treatment related effects can occur in radioembolization. As long as the patient is treated with the correct technique, which includes that no excessive radiation dose be delivered to any organ, the common adverse events after receiving radioactive microspheres are fever, abdominal pain, nausea, vomiting, diarrhoea and fatigue (i.e. postembolization syndrome) [10,28-30]. These effects are in general self-limiting within 1 to 2 weeks, and may be up to grade 3 or 4 (CTCAE v3.0) without direct clinical relevance. Based on the preclinical studies, a similar safety profile is expected for ^166^Ho-RE [22,23].

### Escape medication

Patients will receive oral analgesics (paracetamol up to 4000 mg/24 h) for relief of fever and pain after the administration of microspheres. To reduce nausea and vomiting, patients will receive anti-emetics (ondansetron up to 3 dd 8 mg) during the first 24 hours after administration of the treatment dose. In the case of persisting nausea, metoclopramid (up to 300 mg/24 h) will be used. Patients suffering from diarrhoea will receive loperamide (up to 16 mg/24 h). The vascular contrast agent jodixanol (Visipaque ^®^) may cause renal insufficiency in poorly hydrated patients. All patients will therefore be hydrated. This consists of 1.5 l NaCl 0.9% both prior to and post angiography. Inadvertent delivery of microspheres into organs such as the lungs, stomach, duodenum, pancreas, and gallbladder is associated with serious side effects. To reduce toxicity of the radioactive microspheres in patients with excessive extrahepatic deposition of ^166^Ho-PLLA-MS, the cytoprotective agent amifostine (Ethyol ^®^, up to 200 mg/m ^2 ^for 7 days) may be administered intravenously.

### Statistical considerations

Descriptive statistics (n, mean, standard deviation, median, minimum and maximum) will be calculated for each quantitative variable; frequency counts by category will be made for each qualitative variable. Interim analysis will be performed after every 3 patients. Inclusion of patients in the next cohort will be performed if the Independent Data Monitoring Committee (IDMC) has scrutinized the toxicity data and given permission to proceed.

Two sets of study data will be evaluated: the primary objective will be evaluated in the full analysis set (FAS). The FAS is defined as the set of data generated from the included patients who received at least the safety dose. The secondary objectives will be evaluated in both FAS and per-protocol set (PPS). The PPS is defined as the set of data generated from the included patients who complied with the protocol.

### Monitoring

The IDMC will perform a safety review after each series of treatments of three consecutive patients. The IDMC members have no conflict of interest with the sponsor because they are not involved in the study, nor are they receiving funds. The IDMC will work according to standard operating procedures and will receive reports on a regular basis on all toxicity CTCAE ≥ grade 3 reported for this trial. Recruitment will not be interrupted unless otherwise requested by the chairman of the IDMC. The responsibilities of the IDMC include:

• minimize the exposure of patients to an unsafe therapy or dose

• make recommendations for changes in study processes where appropriate

• endorse continuation of the study

• inform the institutional IEC in the case of toxicity CTCAE ≥ grade 3 and/or when the well-being of the subjects is jeopardized

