### Primary objective

The primary objective of this study is to establish the safety and toxicity profile of treatment with ^166^Ho-PLLA-MS. This profile will be established using the CTCAE v3.0 methodology and will be used to determine the maximum tolerated radiation dose. Any of the following events which are considered possibly or probably related to the administration of ^166^Ho-PLLA-MS will be considered a serious adverse event during the 12 weeks follow-up period:

• Grade 3-4 neutropenic infection (absolute neutrophil count < 1.0 × 10 ^9^/L) with fever > 38.3°C,

• Grade 4 neutropenia lasting > 7 days,

• Grade 4 thrombocytopenia (platelet count < 25.0 ×10 ^9^/L),

• Grade 3 thrombocytopenia lasting for > 7 days,

• Any other grade 3 or 4 toxicity (excluding expected AST/SGOT, ALT/SGPT elevation, elevated bilirubin and lymphopenia) possibly related to study device, using CTCAE v3.0.

• Any life threatening event possibly related to the study device: events as a consequence of inadvertent delivery of ^166^Ho-PLLA-MS into non-target organs like the lung (radiation pneumonitis), the stomach and duodenum (gastric/duodenal ulcer or perforation), the pancreas (radiation pancreatitis), and liver toxicity due to an excessive radiation dose ("radiation induced liver disease" (RILD) [10]).

The haematological and biochemical adverse events as well as RILD will be considered dose limiting toxicity.

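### Escalation review is triggered by treating three patients, with no minimum observation of the last: a dose 20 Gy higher can follow about 1 to 4 weeks (plus review time) into that patient's 12-week follow-up

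*Protocol article*

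**What the plan says.** All references are to the protocol article.

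- **Review trigger.** Monitoring: "The IDMC will perform a safety review after each series of treatments of three consecutive patients". Statistical considerations likewise places an interim analysis after every 3 patients. Neither gives an observation time.
- **Gate.** Statistical considerations allows inclusion in the next cohort once the IDMC "has scrutinized the toxicity data and given permission to proceed". How mature those data must be is not stated.
- **Recruitment.** Monitoring: "Recruitment will not be interrupted unless otherwise requested by the chairman of the IDMC".
- **Escalation rule.** The treatment-dose section moves to the next level when no toxicity of grade 3 or higher has been seen in the cohort of three. The rule carries no time window.
- **Toxicity period.** Primary objective lists events that "will be considered a serious adverse event during the 12 weeks follow-up period", and says that the toxicity profile "will be used to determine the maximum tolerated radiation dose". It then adds: "The haematological and biochemical adverse events as well as RILD will be considered dose limiting toxicity". That last sentence gives no window of its own, so 12 weeks is the only period stated. Follow-up is weekly for those 12 weeks.

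**The concern.** The period over which toxicity is counted and the moment at which escalation may be decided are both stated, and nothing links them. The escalation rule turns on what has been observed. As written, that can be judged on a third patient who has been seen for a small part of follow-up.

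This matters because the article describes the first clinical study of the treatment, and each step adds 20 Gy. Safety profile dates only the postembolization effects, which it says generally settle in 1 to 2 weeks. It gives no onset for radiation-induced liver disease (RILD) or haematological toxicity, which are among the events named as dose limiting. If such an event appears in the third patient after an early review, patients may already have received the higher dose.

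**Working it through.** **1. The plan's own figures.** Sample size: 3 + 3 + 3 + 6 = 15 at least and 4 × 6 = 24 at most, as stated. Dose steps with the stated conversion factor of 15.87 × 10⁻³ J/MBq: 20, 40, 60 and 80 Gy give 1.26, 2.52, 3.78 and 5.04 GBq/kg, matching Table 2. Each escalation is therefore 20 Gy.

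**2. Shortest and longest work-up of the next patient.** Inputs: screening is 0 to 14 days before the first angiography (Screening); the second angiography follows after around 7 and at most 14 days (safety-dose section). I take inclusion to be the screening visit and the treatment dose to be given in the same admission as the safety dose.

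- Shortest: 0 + 7 = 7 days, about 1 week.
- Longest: 14 + 14 = 28 days, 4 weeks.

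Four weeks is the upper limit of the work-up, not a guaranteed minimum.

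**3. Follow-up of the last patient when the next level is first dosed.** With permission r weeks after that patient's treatment, the follow-up is r + 1 to r + 4 weeks. The article does not give r, so every row is an assumption.

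| r (weeks) | Follow-up (weeks) | Share of 12 weeks |
|---|---|---|
| 0 (prompt) | 1 to 4 | 8% to 33% |
| 2 | 3 to 6 | 25% to 50% |
| 4 | 5 to 8 | 42% to 67% |
| 6 | 7 to 10 | 58% to 83% |

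At the review itself, only about r of that patient's 12 weekly visits have taken place.

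**4. Illustration of what early review can miss.** The article gives no toxicity rates or onset times. Assume a 12-week risk p of a qualifying toxicity, uniform onset, the first two patients fully observed, and a fraction f of the third patient's 12 weeks observed. Then P(none seen in three) = (1 − p)² × (1 − p·f).

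| p | f = 1 | f = 4/12 | f = 1/12 |
|---|---|---|---|
| 0.20 | 0.51 | 0.60 | 0.63 |
| 0.33 | 0.30 | 0.40 | 0.44 |
| 0.50 | 0.13 | 0.21 | 0.24 |

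These values show direction and rough scale only. They follow from the assumptions and are not estimates for this device.

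**5. Cost of a hold of W weeks before each of three escalations.** Recruitment runs from October 2009 to January 2011: 427 days (31 October to 1 January) to 487 days (1 October to 31 January), or 61.0 to 69.6 weeks. An even pace is 61.0/24 = 2.54 to 69.6/15 = 4.64 weeks per patient. The net addition is 3 × max(0, W − pace).

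- W = 4: gross 3 × 4 = 12 weeks. Net 0 to 3 × (4 − 2.54) = 4.4 weeks.
- W = 6: gross 3 × 6 = 18 weeks. Net 3 × (6 − 4.64) = 4.1 to 3 × (6 − 2.54) = 10.4 weeks.
- If a late event extends each of the three lower cohorts, each can wait two windows: 6 × 4 = 24 or 6 × 6 = 36 weeks gross.

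The net figures treat the hold as replacing the usual interval between patients, with the next patient's work-up running meanwhile.

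**The case against.** The strongest objection is that this is an omission from a condensed article. Monitoring says that the IDMC follows standard operating procedures, and these, or the full protocol, may fix how much follow-up a review needs. That stands as a caveat. It does not dispose of the point, because the article itself states the review trigger, the gate, the recruitment default, the escalation rule and the follow-up length. The difficulty is what those stated rules allow together.

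The gate is also real. The IDMC must permit inclusion in the next cohort, receives reports of toxicity of grade 3 or higher, and is charged with limiting exposure to an unsafe dose. A reader might infer from the recruitment sentence that patients enter the next level regardless. The text does not support this, since that sentence does not override the need for permission. Permission with almost no delay is the extreme case, which the text allows but does not plan.

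A reader might also argue that two listed events, "Grade 4 neutropenia lasting > 7 days" and "Grade 3 thrombocytopenia lasting for > 7 days", cannot be classified in the third patient at a review within a week of treatment. This adds little. The escalation rule responds to any toxicity of grade 3 or higher, with no duration condition, so such an event blocks simple escalation at onset. What remains is onset after the review.

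Finally, 12 weeks is attached to the serious adverse events, not expressly to the escalation decision. The percentages use it as a yardstick for follow-up and do not show that 12 weeks is the required window. The pig data in the Discussion (only mild effects, at least up to 160 Gy) are reassuring, but come from healthy animals.

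**Conclusion.** The point holds as a weakness in what the plan permits. With prompt permission, the stated rules let a dose 20 Gy higher be given when the last patient of the cohort is about 1 to 4 weeks, plus review time, into a 12-week follow-up. This rests on the stated work-up intervals, on inclusion starting at screening, and on the treatment dose following in the same admission as the safety dose. How often it would happen depends on IDMC discretion and on procedures not shown.

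Two stronger readings are not supported. One is that the final MTD would be wrong: later events are still counted through week 12 and still reach the IDMC, so it need not be. The other is that every cohort must complete 12 weeks before escalation: no sentence requires this, and a justified shorter window can meet the concern. The harm that remains is avoidable exposure at the higher dose. Its size cannot be estimated from the article, which gives neither toxicity rates nor the onset of RILD and haematological events. It should be fixed before the first escalation.

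**What to change.** State in the treatment-dose section, Statistical considerations and Monitoring that the IDMC may permit escalation only after the last treated patient of the cohort has completed a fixed minimum observation. Four weeks is one option. Six weeks is another, and coincides with the scheduled week-6 assessment. Justify the choice against the expected onset of RILD and haematological toxicity.

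Apply the hold to escalation only, not to extending a cohort at the same dose. Let screening continue meanwhile, and say whether screening counts as inclusion, since inclusion currently waits for permission. Keep reporting later events through week 12 to the IDMC, with power to halt or step down the dose. If IDMC procedures already set a minimum, one sentence repeating it is enough.

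The cost is wording in three sections and some time: 12 weeks of holds at a 4-week window (net about 0 to 4) or 18 weeks at 6 (net about 4 to 10). Late events that extend cohorts add more, up to 24 or 36 weeks of holds if all three lower cohorts are affected. In return, the guaranteed observation of the last patient rises from about 1 week plus review time to at least 4 or 6 weeks.

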### Ethical considerations

The study will be conducted according to the principles of the Declaration of Helsinki (version 9.10.2004) and in accordance with the Medical Research Involving Human Patients Act (WMO), the requirements of International Conference on Harmonization - Good Clinical Practice. The study protocol has been approved by the IEC and by the institutional Radiation Protection Committee.

## Discussion

The HEPAR trial is a phase I study to evaluate the safety and toxicity profile of ^166^Ho radioembolization. Secondary endpoints are tumour response, biodistribution assessment, performance status, quality of life and comparison of the biodistributions of the ^99m^Tc-MAA scout dose and the ^166^Ho-PLLA-MS safety dose.

With regard to the method of administration, viz. through a catheter placed in the hepatic artery, the in-vivo characteristics (no significant release of radionuclide), and the mechanism of action (local irradiation of the tumour), ^166^Ho-PLLA-MS constitute a device analogous to the ^90^Y microspheres, which are currently applied clinically. ^166^Ho-PLLA-MS only differ in the radioisotope and the device matrix that are used. In a toxicity study in pigs on ^166^Ho-RE, it has been demonstrated that (healthy) pigs can withstand extremely high liver absorbed doses, at least up to 160 Gy [23]. During these animal experiments, only very mild side effects were seen: slight and transitory inappetence and somnolence, which may well have been associated with the anaesthetic and analgesic agents that had been given and not necessarily with the microsphere administration. It is plausible that this low toxicity profile is caused by the inhomogeneous distribution of ^166^Ho within the liver after intra-arterial injection, as was observed on MRI and SPECT images. The current study will investigate whether a similar distribution pattern can also be observed in human subjects and whether this inhomogeneous distribution is concentrated around the tumour sites.

Hepatic arterial injection with ^99m^Tc-MAA and subsequent scintigraphic imaging is widely used to predict the biodistribution of ^90^Y microspheres, prior to the actual radioembolization procedure. Its accuracy can however be disputed. In our centre, we have observed that patients with a borderline lung shunt fraction of 10% to 19%, as calculated using the ^99m^Tc-MAA images (approximately 24% of all patients, all of whom were instilled a by 50% reduced amount of radioactivity), had no signs of lung shunting on post- ^90^Y-RE Bremsstrahlung images. In these cases, it seems that the ^99m^Tc-MAA-scan had false-positively predicted extrahepatic spread. This may be explained by the fact that ^99m^Tc-MAA differs in many aspects from the microspheres that are used. Shape, size, density, in-vivo half-life, and number of ^99m^Tc-MAA particles do not resemble the microspheres in any way [13,31]. In addition, free technetium that is released from the MAA particles can disturb the (correct) assessment of extrahepatic spread. We hypothesize that a small safety dose with low-activity ^166^Ho-PLLA-MS will be a more accurate predictor of distribution than ^99m^Tc-MAA. The unique characteristics of ^166^Ho-microspheres, in theory, allow a more accurate prediction of the distribution with the use of scintigraphy and MRI. In this study, we chose to perform both an injection with ^99m^Tc-MAA and administration of a safety dose of ^166^Ho-PLLA-MS. The respective distributions of the ^99m^Tc-MAA and the ^166^Ho-PLLA-MS safety dose will be compared with the distribution of the treatment dose of ^166^Ho-PLLA-MS by quantitative analysis of the scintigraphic images.

Both commercially available ^90^Y-MS products are approved by the Food and Drug Administration (FDA) and European Medicines Agency as a medical device and not as a drug. Radioactive microspheres are a medical device since these implants do not achieve any of their primary intended purposes through chemical action within or on the body and are not dependent upon being metabolized for the achievement of their primary intended purpose. In accordance with the definition of a medical device by the FDA and in analogy with the ^90^Y-MS, we consider the ^166^Ho-PLLA-MS to be a medical device [32]. The Dutch medicine evaluation board has discussed this issue (13 July 2007) and has concluded that the microspheres are indeed to be considered as a medical device.

One important issue concerning the resin-based SIR-Spheres ^® ^is the relatively high number of particles instilled (>1,000 mg), since this may sometimes be associated with macroscopic embolization as observed during the fluoroscopic guidance [28,33]. Several authors have reported stasis of flow during administration of resin microspheres and were forced to end the procedure prematurely because of the risk of backflow, hence extrahepatic deposition of a part of the dosage [28,34,35]. The specific activity of the ^166^Ho-PLLA-MS is considerably higher than that of the resin microspheres (≤450 and 50 Bq/microspheres, respectively). However, in order to obtain an equivalent absorbed dose, the total amount of radioactivity of the administered microspheres in ^166^Ho radioembolization needs to be 3 times higher than in ^90^Y radioembolization, due to the shorter physical half-life of ^166^Ho. Even so, compared with the resin ^90^Y microspheres, in ^166^Ho radioembolization considerably less microspheres (≤600 mg) are used to obtain an equivalent radiation dose, resulting in a lower risk of stasis or backflow during administration [9,29]. A further issue is that ^90^Y microspheres can not be visualized under fluoroscopy during injection. Manufacturers of resin ^90^Y microspheres state that their microspheres are to be administered with water for injection alternated with non-ionogenic contrast [36]. As a result, the operating physician cannot detect stasis or backflow of microspheres until he has switched from injecting microspheres to injecting the contrast agent. Holmium microspheres, on the contrary, are administered in a mixture of 50% saline and 50% non-ionogenic contrast under constant fluoroscopic imaging, which ensures constant control over the microspheres during injection [37]. However, continuous fluoroscopic imaging during microsphere administration may comprise an increased radiation dose delivered to the patient, specifically the abdominal skin, during the procedure. 	

If this phase I trial provides sufficient data to prove that ^166^Ho-PLLA-RE has an acceptable safety and toxicity profile, further studies will be needed. The next step will be an efficacy study in a larger number of patients. The primary endpoints of that study will be tumour response and survival.

## Appendix 1 - Eligibility criteria for ^166^Ho-RE

### Inclusion criteria

• Signed informed consent letter

• Age >18 years

• Liver-dominant metastases without standard treatment options. Liver-dominant disease is defined as the diameter of all metastases in the liver to be more than 200% of the sum of the diameters of all soft tissue lesions outside the liver.

• Life expectancy of ≥12 weeks

• World Health Organisation (WHO) Performance status 0-2

• ≥1 measurable lesions of ≥10 mm in the longest diameter by spiral computed tomography (CT) (5 mm slice thickness)

• Negative pregnancy test for women

### Exclusion criteria

• Brain metastases or spinal cord compression, unless irradiated at least 4 weeks prior to the date of the experimental treatment, and stable without steroid treatment for at least 1 week

• Radiation therapy within the last 4 weeks before study enrolment

• Patient has received chemotherapy within 4 weeks prior to enrolment

• Major surgery within 4 weeks, or incompletely healed surgical incision before enrolment

• Any unresolved toxicity greater than National Cancer Institute (NCI), Common Terminology Criteria for Adverse Events (CTCAE version 3.0)[26] grade 2 from previous anti-cancer therapy

• Alanine aminotransferase (ALT), aspartate aminotransferase (AST), or alkaline phosphatase (ALP) >5× Upper Limit of Normal (ULN), serum bilirubin >1.5× ULN or serum creatinine >185 µmol/L

• Leukocytes <4.0 10 ^9^/l and/or platelet count <150 10 ^9^/l

• Significant cardiac event (e.g. myocardial infarction, superior vena cava (SVC) syndrome, New York Heart Association (NYHA) classification of heart disease ≥2 within 3 months before entry, or presence of cardiac disease that, in the opinion of the investigator, increases the risk of ventricular arrhythmia

• Pregnancy or breast feeding

• Comorbidity with a grave prognosis (estimated survival <3 months) and/or worse than the basic disease for which the patients will be included in the study

• Abnormalities of the bile ducts (such as stents) with an increased chance of infection

• Diseases with an increased chance of liver toxicity, such as primary biliary cirrhosis or xeroderma pigmentosum

• Patients who are declared incompetent or have a psychiatric disorder that makes a comprehensive judgement impossible, such as psychosis, hallucinations and/or depression

• Previous enrolment in the present study or previous treatment with radioembolization

• Treatment with an investigational agent within 42 days prior to enrolment

• Female patients who are not using an acceptable method of contraception or are less than 1 year postmenopausal or surgically sterile during their participation in this study (from the time the consent form is signed) to prevent pregnancy

• Male patients who are not surgically sterile or do not use an acceptable method of contraception during their participation in this study to prevent pregnancy in a partner

• Evidence of portal hypertension, splenomegaly or ascites

• Body weight >150 kg

• Active hepatitis (B and/or C)

• Liver weight >3 kg (determined by software using CT data)

• Allergy for intravenous contrast agent used (Visipaque ^®^)

• General MRI contra-indications (severe claustrophobia, metal implants, implanted pacemaker and/or neurostimulators)

• Patients who have arterial variations that will not allow whole liver treatment by a single administration via the hepatic artery
